### Study objectives

The primary objective is to evaluate trends in post-filter iCa2+, pre-filter iCa effluent iCa2+ and total calcium, systemic iCa2+, and total calcium concentration over time in different RCA-CRRT modes.

The secondary objectives are to analyze the amount of citrate used in different modes to achieve the desired anticoagulant effect in current clinical practice, and to assess the incidence of new-onset metabolic complications (hypercalcemia, hypocalcemia, metabolic acidosis, metabolic alkalosis, citrate accumulation, hypernatremia, hyponatremia). The incidence of metabolic complications will be calculated as the number of new-onset metabolic complication events per 100 CRRT days. In this study, citrate accumulation is defined as the presence of a total serum calcium/ionized calcium ratio > 2.5.

### Sample size

According to the results of our pilot study, the post-filter iCa concentration was 0.44 mmol/L in the CVVHD mode and 0.305 mmol/L in the CVVH mode. Assuming a standard deviation of 0.2 mmol/L, taking a *α* = 0.05 and a *β* = 0.10, the required sample size is 26 cases. Thirty patients will be included in the study considering the possible loss of follow-up.

### Statistical analysis

Data will be analyzed using SPSS 23.0 statistical software (IBM Co., NY). Continuous variables will be presented as means and standard deviations (for normal distribution) or medians and interquartile ranges (for non-normal distribution). A paired *t*-test will be used for normally distributed variables, and the Wilcoxon signed-rank test will be used for non-normally distributed variables. Categorical variables will be presented as numbers and percentages and analyzed using the *χ*^2^-test or Fisher’s exact tests, as appropriate. For the crossover design, we will specifically examine both carry-over and period effects. The carry-over effect will be assessed by comparing the sum of the outcomes between sequences using a t-test or Mann-Whitney U test depending on data distribution. The sequence of interventions will be randomly assigned to minimize potential period effects. A two-sided *p* < 0.05 will be considered a statistically significant difference.

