### CRRT parameter setting and management

PrismaFlex (Baxter Investment Co., Ltd, Chicago, IL) CRRT device and AN69 ST150 hemofilters (Baxter Investment Co., Ltd, Shanghai, China) will be used. Vascular access will be established by inserting a double-lumen catheter (SCW Medication Ltd, certification number: 20173664588, 12 Fr, 20 cm) into either the femoral or internal jugular vein. CRRT will be ended for any of the following reasons: achievement of therapeutic goals; coagulation of the filter; transmembrane pressure continuously > 250 mmHg; or continuous treatment for 48 h (to replace pipeline and filter).

This study is a before-after design in the same patient; each patient will receive both continuous veno-venous hemofiltration (CVVH) and continuous veno-venous hemodialysis (CVVHD) at least once. Patients will be initially randomized into either the CVVHD or CVVH groups and then crossed over to the other group during the second CRRT session. Regardless of whether CVVH or CVVHD is used, the initial settings will be as follows: blood flow rate of 150 ml/min, 4% sodium citrate flow rate of 230 ml/h, 10% calcium gluconate infusion rate of 10 ml/h, and a 5% sodium bicarbonate infusion rate (ml/h) of dialysate/replacement fluid × 0.0625 − 120. The therapeutic dose will be 30 ml/kg/h depending on the mode investigated, that is, a dialysate rate (ml/h) of 30 ml × body weight (kg) in the setting of CVVHD; on the other hand, the replacement fluid rate (ml/h) will be 30 ml × body weight (kg) in the setting of CVVH.

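### The only test stated for categorical outcomes assumes independent groups, although every patient receives both modes, and it does not fit complications defined per 100 CRRT days

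*Protocol article*

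**What the plan says.** CRRT parameter setting and management describes the design: "This study is a before-after design in the same patient", with each mode received one or more times. On allocation: "Patients will be initially randomized into either the CVVHD or CVVH groups and then crossed over to the other group during the second CRRT session".

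The same section lets a session end for several reasons: "achievement of therapeutic goals; coagulation of the filter; transmembrane pressure continuously > 250 mmHg; or continuous treatment for 48 h". Session length is therefore variable.

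Study objectives lists seven new-onset metabolic complications as a secondary objective and defines the measure: "The incidence of metabolic complications will be calculated as the number of new-onset metabolic complication events per 100 CRRT days".

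Statistical analysis respects the pairing for continuous variables: "A paired *t*-test will be used for normally distributed variables, and the Wilcoxon signed-rank test will be used for non-normally distributed variables". The next sentence, on categorical variables, does not: "Categorical variables will be presented as numbers and percentages and analyzed using the *χ*^2^-test or Fisher’s exact tests, as appropriate". No paired categorical test and no method for event rates is named. The significance rule is general: "A two-sided *p* < 0.05 will be considered a statistically significant difference".

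**The concern.** There are two separate mismatches.

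**Pairing.** Chi-square and Fisher's exact test treat the CVVH and CVVHD results as coming from different patients. Here the same patients supply both. With positive within-patient correlation and one session per mode, the assumed standard error is too large, so a real difference between modes can be missed.

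**Exposure.** A rate per 100 CRRT days needs events and time at risk. A table of numbers and percentages drops the time. If sessions run longer in one mode, the percentage with an event differs even when the rates are equal. This is plausible under the study's own reasoning: the Introduction and the Figure 1 legend say that CVVHD may raise post-filter ionized calcium and so affect citrate anticoagulation, and clotting ends a session.

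The Discussion section of the article promises data on citrate-related adverse effects by mode, so this comparison will be read.

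**Working it through.** **1. The plan's own figure is paired.** Inputs from Sample size: means 0.44 and 0.305 mmol/L (difference 0.135), SD 0.2, alpha 0.05, beta 0.10. Take 0.2 as the SD of the within-patient difference (the article does not say which SD it is).

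- Normal approximation: ((1.960 + 1.282) × 0.2 / 0.135)² = 23.06, so 24.
- Noncentral t, two-sided: power 0.899 at n = 25 and 0.911 at n = 26.
- Two independent groups would need 47 per arm.

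The stated 26 is the two-sided paired t-test. Planning and continuous analyses are paired; the categorical analysis is not.

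**2. Effect of ignoring the pairing.** Assumptions: 30 patients, one session per mode, event probability p = 0.3 in both modes, correlation ρ between a patient's two yes/no outcomes.

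- Variance assumed by chi-square: 2p(1−p)/n = 0.42/30 = 0.0140, SE 0.118.
- True variance: 2p(1−p)(1−ρ)/n. At ρ = 0.4 this is 0.252/30 = 0.0084, SE 0.092.
- The effective cut-off is 1.96/√(1−0.4) = 2.53, a two-sided error of about 1.1% instead of 5%.

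Simulation (20,000 trials) agrees:

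| ρ (binary scale) | Chi-square | Fisher |
|---|---|---|
| 0 | 5.0% | 2.7% |
| 0.2 | 2.7% | 1.1% |
| 0.4 | 1.1% | 0.5% |
| 0.6 | 0.3% | 0.1% |

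With correlation placed on a latent normal scale instead, chi-square rejects about 1.7% (latent 0.5) and 0.7% (latent 0.7).

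**3. Power under pairing** (simulation, 30 pairs, latent correlation):

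| Assumed incidence | Latent correlation | Chi-square | Exact McNemar | Mid-p McNemar |
|---|---|---|---|---|
| 20% vs 45% | 0.2 | 55% | 47% | 57% |
| 20% vs 45% | 0.5 | 55% | 56% | 66% |
| 20% vs 45% | 0.7 | 56% | 66% | 76% |
| 5% vs 15% | 0.5 | 22–23% | 9% | 18% |

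The gain depends on common events, appreciable correlation and the mid-p version. For rare events McNemar has no power advantage over chi-square.

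**4. Effect of ignoring exposure.** Assume the same true rate λ per CRRT day in both modes, sessions of 48 h (2 days) in one and 24 h (1 day) in the other, and no within-patient correlation. The proportion with at least one event is 1 − exp(−λt).

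- λ = 0.2: 1 − exp(−0.4) = 33% against 1 − exp(−0.2) = 18%.
- λ = 0.4: 1 − exp(−0.8) = 55% against 1 − exp(−0.4) = 33%.

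| λ per day | Chi-square | Fisher | Exact McNemar | Mid-p McNemar |
|---|---|---|---|---|
| 0.2 | 26% | 18% | 16% | 23% |
| 0.4 | 41–42% | 31% | 31% | 39% |

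These are rejection rates when the outcome as defined, events per 100 CRRT days, does not differ. With equal 48 h sessions chi-square stays near 5% (4.5% and 5.0%). Pairing alone does not cure this; the analysis needs time at risk.

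**The case against.** **The categorical sentence never mentions metabolic complications.** This stands. A rate is not literally a categorical variable, and the article promises only to calculate it. A reader might infer that the plan commits to testing complications by chi-square; the text does not say so. The sentence could also serve baseline items such as sex or comorbidities, for which independent-group tests between sequences are suitable. What remains is that it is the only method given for anything non-continuous, it carries no restriction to baseline tables, and it follows directly after paired tests for the mode comparison.

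**The detail may sit in a fuller analysis plan.** That would excuse silence about a rate model. It does not excuse a stated test that contradicts the design. Reading the chi-square test as McNemar's does not help, because Fisher's exact test, its stated alternative, is for independent groups.

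**The damage may be small.** In part this stands. With one session per mode and positive correlation, the pairing error is conservative, so a reader should not infer that it creates false safety signals. False positives need unequal session lengths, or repeated events or sessions counted as independent, and the article quantifies none of these. Nor does a paired test always gain power, as the table above shows.

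**Exposure cannot be capped.** It is tempting to read the design as 30 sessions per mode and at most 60 CRRT days (30 × 48 h). The article allows more than one session per mode and a new circuit after clotting, so neither figure is a maximum. Further sessions would add clustering that chi-square and Fisher also ignore.

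**Conclusion.** The point holds as a mismatch between the stated categorical tests and both the crossover design and the definition of the complication rate. Used as written for a between-mode comparison, the method has the wrong error rate: about 1.7% to 0.7% instead of 5% from ignored pairing, and about 26% to 42% from ignored exposure if sessions run 48 h against 24 h. Against chi-square power of about 55% at 20% vs 45%, exact McNemar gives 56% to 66% and mid-p McNemar 66% to 76%.

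Every incidence, rate, correlation and session length behind these figures is an assumption, as is one session per mode. They show direction and plausible size and do not predict this trial.

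Severity: should be fixed. Only secondary outcomes are touched. A reader might infer that the main result is at risk, but ionized calcium and citrate dose are continuous and get paired tests, and the sample size of 26 reproduces on a paired basis.

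**What to change.** Amend the Statistical analysis section as follows.

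- **Complications per 100 CRRT days, between modes:** Poisson or negative-binomial model with log(CRRT time) as offset, mode and period as fixed effects, and patient as cluster (GEE or random effect). Report the rate ratio with its 95% confidence interval.
- **Other yes/no outcomes between modes, such as filter clotting:** mid-p McNemar with one session per mode, or conditional logistic regression stratified by patient when there are several.
- **Chi-square and Fisher's exact test:** keep for baseline tables between sequences only.

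The cost is analysis wording. Sample size and patient management do not change, and filter lifetime and treatment time are already to be recorded or used. The downside is that with few events the rate model may be unstable and its intervals wide.

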### Randomization, blind, and allocation concealment

The study is a prospective, randomized, crossover-designed study. Random assignment is based on a computer-generated random number table using a concealed sealed and numbered envelope procedure to assign patients to one of the two study groups prior to the first CRRT mode. Treatment allocation is blinded to patients and other investigators, with the exception of bedside clinicians and nurses. Investigators who perform the blood gas analysis are unaware of the details of the trials.

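### The plan promises to examine period effects, but its named tests have no period term, and its carry-over test is too weak to show that carry-over is absent

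*Protocol article*

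**What the plan says.** The Statistical analysis section of the protocol article assigns continuous variables to a paired *t*-test or, if non-normal, a Wilcoxon signed-rank test. It then says that carry-over and period effects will both be looked at specifically.

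- **Carry-over** has a procedure: "The carry-over effect will be assessed by comparing the sum of the outcomes between sequences", by t-test or Mann-Whitney U test.
- **Period** has none. The only sentence is "The sequence of interventions will be randomly assigned to minimize potential period effects".
- **Allocation** (Randomization, blind, and allocation concealment): "Random assignment is based on a computer-generated random number table using a concealed sealed and numbered envelope procedure". Neither a ratio nor blocking is stated or ruled out.
- **Sessions** (CRRT parameter setting and management): "each patient will receive both continuous veno-venous hemofiltration (CVVH) and continuous veno-venous hemodialysis (CVVHD) at least once", with the switch of mode at the second session.
- **Covariates** (Discussion): adjustment is promised for acid-base and biochemical parameters. Period and sequence are not listed.
- **Washout** (CRRT parameter setting and management): absence of carry-over is argued from the short half-life of citrate and the time taken to change the circuit.

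**The concern.** A paired test on the within-patient difference treats every pair alike, whichever mode came first. If post-filter ionized calcium (iCa) shifts between the first and second session for reasons unrelated to mode, the shift enters the difference with opposite signs in the two sequences. With equal sequences it cancels from the mean but stays in the estimated variance. With unequal sequences part of it stays in the mode estimate. Randomising the order does not change this for the sample actually obtained. The promised examination of period therefore has no counterpart in the tests named.

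The carry-over test has a different weakness. It compares patient totals between two groups of at most about 15, so between-patient variation, which the crossover was chosen to remove, returns in full. The risk is that a non-significant result is read as showing that there is no carry-over.

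**Working it through.** **Inputs.** From Sample size: "the post-filter iCa concentration was 0.44 mmol/L in the CVVHD mode and 0.305 mmol/L in the CVVH mode", so the planned difference is δ = 0.44 − 0.305 = 0.135 mmol/L; "Assuming a standard deviation of 0.2 mmol/L"; "taking a *α* = 0.05 and a *β* = 0.10"; 26 required and 30 enrolled. From Statistical analysis: "A two-sided *p* < 0.05 will be considered a statistically significant difference". The size of a period effect, the within-patient correlation ρ and the use of blocking are not given; they are assumed below and shown over a range.

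**1. The plan's own figure.** For a paired t-test with 0.2 as the SD of the within-patient difference, the normal approximation gives (1.960 + 1.282)² × (0.2/0.135)² = 23.06, so 24. The exact noncentral t gives power 0.899 at n = 25 and 0.911 at n = 26. The stated 26 reproduces on this reading of the SD, which is used below.

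**2. Period in the paired test.** Let π be the change from session 1 to session 2 that is common to both modes, and D = CVVHD − CVVH within a patient. Then D has mean δ + π if CVVH came first and δ − π if CVVHD came first. With n₁ and n₂ pairs in these sequences, the paired estimate has mean δ + π(n₁ − n₂)/(n₁ + n₂).

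- At 13:13 the bias is 0.
- At 17:9 it is π × 8/26 = 0.308π. The sign depends on which sequence is larger and on the direction of the shift.

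Simulation of the paired t-test, 26 pairs, SD of D = 0.2:

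| Assumed π (mmol/L) | 13:13 power | 13:13 type I error | 17:9 bias (mmol/L) | 17:9 type I error |
|---|---|---|---|---|
| 0 | 0.91 | 0.05 | 0 | 0.05 |
| 0.05 | 0.90 | 0.043 | 0.015 | 0.059 |
| 0.10 | 0.865 | 0.029 | 0.031 | 0.079 |
| 0.135 | 0.82 | 0.018 | 0.042 | 0.095 |

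**3. The period-adjusted estimate.** Average the two sequence means of D: ½[(δ + π) + (δ − π)] = δ, whatever π is. Its standard error is ½ × 0.2 × √(1/n₁ + 1/n₂), with 24 degrees of freedom.

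- At 13:13: 0.1 × √(2/13) = 0.039, the same as 0.2/√26. Power is 0.91 for every π.
- At 17:9: 0.1 × √(1/17 + 1/9) = 0.041. Power is 0.88, type I error 0.05, bias 0.

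**4. Chance of an uneven split.** If allocation is simple 1:1 without blocks, a split of 17:9 or worse among 26 has probability 2 × P(X ≤ 9), X ~ Binomial(26, 0.5), which is 0.17.

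**5. Power of the carry-over test.** If SD(D) = 0.2, the SD of a patient's sum is 0.2 × √[(1 + ρ)/(1 − ρ)]. Take a carry-over difference between sequences of 0.135 and 15 patients per sequence:

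| ρ | SD of sum | SE = SD × √(2/15) | Power |
|---|---|---|---|
| 0.3 | 0.273 | 0.100 | 0.26 |
| 0.5 | 0.346 | 0.126 | 0.18 |
| 0.7 | 0.476 | 0.174 | 0.12 |

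If 0.2 is instead the SD of a single measurement, power is 0.24 at ρ = 0 and 0.16 at ρ = 0.75. At ρ = 0.5 the difference detectable with 80% power is 0.37 mmol/L, and 0.37/0.135 = 2.7 times the planned effect. Having 90% power for 0.135 would take about 139 patients per sequence.

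**The case against.** The article does not neglect period: it undertakes to examine it, and its Discussion promises covariate adjustment, which needs some model beyond a paired test. It condenses a fuller protocol, and a statistical analysis plan may exist, so the absence of a detailed period procedure is not in itself a fault. That stands. What remains is narrower: the article does fix the tests for continuous outcomes, and those tests cannot deliver what the same paragraph promises.

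A large period shift is also not established. Every session starts from the same initial settings, and post-filter iCa is measured two hours into each new circuit. A shift of 0.10 mmol/L would be 74% of the planned effect (0.10/0.135). With equal sequences the paired test is unbiased and conservative. All of this is accepted and limits the size of the point.

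A reader might infer more than the documents support:

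- **That allocation is unblocked.** The article does not say, so the probability of 0.17 is conditional on that assumption.
- **That power falls to 0.84 at a shift of 0.10.** Putting the inflated SD √(0.2² + 0.1²) = 0.224 into the usual power formula gives this. At 13:13, however, the period term cancels from the mean and inflates only the estimated SD, so the correct figure is about 0.865.
- **That losing one-session patients biases the result.** They contribute nothing to a paired test, but selection on iCa is not shown, a within-patient contrast among completers is not automatically biased, and four extra patients are enrolled for loss.
- **That the carry-over test decides the analysis.** The plan gives it no such role, and its washout argument does not depend on the test.

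**Conclusion.** The point holds in a limited form. The tests named for continuous outcomes have no period term, so random order alone does not fulfil the promise to examine period. For assumed shifts of 0.05 to 0.135 mmol/L, the cost is up to 0.09 of power with equal sequences (0.91 to 0.82). At 17:9 it is a bias of 0.015 to 0.042 mmol/L with type I error of 0.059 to 0.095. These figures rest on 26 complete pairs, an SD of the difference of 0.2 and a period shift common to both modes; if there is no shift, there is no harm.

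The carry-over test has roughly 12–26% power for a carry-over as large as the planned effect (15 per sequence, ρ from 0.7 to 0.3). A non-significant result would therefore say almost nothing. This does not suggest that carry-over is present; the washout argument may well be sound.

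The change is worth making because it is nearly free. It is an improvement to the analysis, not a flaw that invalidates the design.

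**What to change.** 1. In Statistical analysis, replace the paired test for continuous outcomes with a period-adjusted crossover analysis. One option is a linear mixed model with mode, period and sequence as fixed effects and patient as a random effect, which can also use one-session patients and repeat circuits. A crossover t-test adjusted for period is a simpler alternative. Report the mode difference with its 95% CI.
2. Report the between-sequence carry-over contrast as an estimate with a confidence interval. Rest the case for no carry-over on the washout argument already given under CRRT parameter setting and management, not on a non-significant test.
3. State whether the sequence list is blocked 1:1.

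Cost: a few sentences and one degree of freedom. If there is no period effect and the sequences end unequal, a little power is lost (0.91 to 0.88 at 17:9); with equal sequences the loss is negligible. The number of patients does not change.

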### Randomization, blind, and allocation concealment

The study is a prospective, randomized, crossover-designed study. Random assignment is based on a computer-generated random number table using a concealed sealed and numbered envelope procedure to assign patients to one of the two study groups prior to the first CRRT mode. Treatment allocation is blinded to patients and other investigators, with the exception of bedside clinicians and nurses. Investigators who perform the blood gas analysis are unaware of the details of the trials.

### Data management

The research data will be accessible only to members of the research team. All data collected will be recorded in the patient’s file and securely stored in a locker. After the completion of the study, all case report forms will be archived. Electronic files will be password-protected to ensure confidentiality. Both paper and electronic files will be retained per the hospital’s policy on the retention and disposal of patient records.

## Discussion

Post-filter iCa level is crucial for adjusting the citrate dose during RCA-CRRT. However, there is a lack of clinical data demonstrating the effects of different CRRT modes on ionized and total serum calcium levels in patients receiving RCA-CRRT with a calcium-containing replacement solution. We hypothesize that post-filter iCa concentration is higher in CVVHD than in CVVH under RCA-CRRT using a calcium-containing replacement solution. If this hypothesis is true, patients may require a higher citrate dose, thereby increasing the risk of citrate-related adverse effects. This study will expand previous work and provide new data regarding the impact of different RCA-CRRT modes on iCa, citrate dose, and citrate-related adverse effects.

While directly measuring citrate and calcium concentrations in the ultrafiltrate would provide a more controlled assessment of solute removal across different CRRT modes, our study aims to evaluate the clinical implications of citrate removal in actual patient care settings. The patient-based approach allows us to observe how variations in citrate removal affect circuit survival and safety parameters under real clinical conditions, including the influence of individual patient factors. This design better reflects the practical challenges and outcomes in routine clinical practice, though we acknowledge it introduces more variability in our measurements. The trade-off between controlled laboratory conditions and clinical relevance was carefully considered in our study design, and we chose to prioritize clinical applicability of our findings.

The iCa levels can be influenced by multiple factors including blood pH, acid-base status, and phosphate levels. To consider these potential confounding factors, we will collect comprehensive blood gas analysis data and biochemical parameters throughout the CRRT sessions. The crossover design of our study will help minimize between-subject variations, as each patient will serve as their own control. Furthermore, we will include these parameters as covariates in our statistical analysis to adjust for their potential effects on iCa levels. This comprehensive analytical approach will strengthen the reliability of our conclusions despite the complex nature of factors affecting iCa homeostasis.

There are several limitations to this study. First, it will only compare the differences in iCa changes between CVVH and CVVHD at each time point, thus not providing information on iCa concentration changes in combined modes (e.g. continuous veno-venous hemodiafiltration, CVVHDF) with varying dialysate and replacement fluid ratios. In other words, this study focuses exclusively on CVVH and CVVHD modes. While CVVHDF is increasingly used in severe AKI patients, we chose CVVH and CVVHD as our initial investigation platforms to establish the fundamental principles in more controlled settings. This strategic approach will serve as a stepping stone for future studies investigating more complex CRRT modalities such as CVVHDF. Second, plasma citrate concentrations will not be measured in this study, making it impossible to directly compare differences in plasma citrate concentrations.

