## Introduction

Over the past decade, the prevalence of acute kidney injury (AKI) has increased significantly. The Kidney Disease Improving Global Outcomes (KDIGO) guidelines indicate that more than 50% of patients in the intensive care unit (ICU) have AKI, with approximately 10% of them requiring renal replacement therapy (RRT) [1,2]. Regional citrate anticoagulation (RCA) is widely used in continuous renal replacement therapy (CRRT) due to its low risk of bleeding and extended filter life [3–11].

Ionized calcium (iCa) is a crucial cofactor activating the coagulation cascade. Citrate acts as an anticoagulant by chelating iCa to form a stable calcium-citrate complex [12–14]. Post-filter iCa level is crucial for the adjustment of the citrate dose: the citrate dose is initially set based on an appropriate citrate dose/blood flow ratio and subsequently adjusted according to the post-filter iCa concentration to maintain a target iCa between 0.20 and 0.40 mmol/L in the circuit (equivalent to a blood citrate concentration of 3–4 mmol/L) in the clinical practice [15,16].

Commercial calcium-containing replacement solutions are increasingly used in CRRT and have a higher iCa concentration than conventional replacement solutions [17–19]. Due to the different mechanisms of solute removal, there could theoretically be apparent differences in post-filter iCa and even systemic calcium when different CRRT modalities are used [20]. For example, in hemodialysis, solutes move with a concentration gradient, and a high concentration of iCa in the dialysate may gradually diffuse into the blood, increasing post-filter iCa (Figure 1A); in contrast, in hemofiltration, the solute and solvent move simultaneously with the pressure gradient, and the post-filter iCa concentration is unlikely to increase (Figure 1B). Since the post-filter iCa concentration is the basis for adjusting the dose of citrate, the potential difference in the post-filter iCa concentration under the different CRRT modalities using calcium-containing replacement solutions may lead to markedly different citrate dosages, even a different incidence of adverse events such as citrate accumulation and citrate toxicity [21–24].

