### Data collection and follow-up

Figure 2 illustrates the process of the entire study. Clinical information will be collected prior to the initiation of CRRT. This includes gender, age, weight, baseline blood urea nitrogen, serum creatinine, urine output, comorbidities, Acute Physiology and Chronic Health Evaluation (APACHE)-II scores, Sequential Organ Failure Assessment (SOFA) score, hemoglobin, platelets, serum total calcium, and ionized calcium. Renal function will be classified according to KDIGO criteria [2].

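### Adjusting iCa for pH, acid-base status and phosphate measured during the sessions may not estimate the total mode effect, and the plan does not say whether the adjusted or unadjusted result is primary

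*Protocol article*

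**What the plan says.** The Discussion states that "The iCa levels can be influenced by multiple factors including blood pH, acid-base status, and phosphate levels". To deal with this, "we will collect comprehensive blood gas analysis data and biochemical parameters throughout the CRRT sessions", and then "we will include these parameters as covariates in our statistical analysis to adjust for their potential effects on iCa levels". The text presents this adjustment as strengthening the conclusions.

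The Statistical analysis section names different tools for continuous variables: a paired t-test under normality, otherwise the "Wilcoxon signed-rank test will be used for non-normally distributed variables". It mentions no covariate model.

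Other sections bear on the choice:

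- **Assignment** (CRRT parameter setting and management): "Patients will be initially randomized into either the CVVHD or CVVH groups and then crossed over to the other group during the second CRRT session".
- **Primary outcome** (Abstract, Methods): the between-mode difference in iCa, by sampling site and over time.
- **Secondary objective** (Study objectives): "to assess the incidence of new-onset metabolic complications (hypercalcemia, hypocalcemia, metabolic acidosis, metabolic alkalosis, citrate accumulation, hypernatremia, hyponatremia".
- **Expected consequence of mode** (Introduction): a difference in post-filter iCa "may lead to markedly different citrate dosages, even a different incidence of adverse events such as citrate accumulation and citrate toxicity".
- **Titration** (Table 1): the citrate rate is changed according to post-filter iCa, with the first assessment two hours after the start.

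**The concern.** The order of the modes is randomised and each patient receives both. A value that arises after a mode has started cannot confound the comparison of modes; it either follows from the mode or varies by chance. If it follows from the mode and also influences iCa, holding it constant removes or distorts part of the effect that the study sets out to measure. If an unmeasured aspect of the patient's condition drives both the covariate and iCa, conditioning can also introduce a bias that the randomised contrast does not have.

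The second problem is that there are two analyses with no stated order between them. The Statistical analysis section supports an unadjusted paired test, while the Discussion promises adjustment. If the two results differ, nothing in the text prevents the choice being made after the data are seen.

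**Working it through.** **1. The plan's own figure.** From the Sample size section: means 0.44 (CVVHD) and 0.305 (CVVH), so the difference is 0.44 - 0.305 = 0.135 mmol/L; SD 0.2; alpha 0.05, two-sided; power 0.90. Taking 0.2 as the SD of the within-patient difference:

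- Normal approximation: n = (0.2 × (1.960 + 1.282) / 0.135)² = 23.06, so 24.
- Noncentral t: n = 25 gives 89.9% power and n = 26 gives 91.1%, so 26.

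The stated 26 reproduces, and it does so on an unadjusted paired contrast.

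**2. When the covariates are measured.** The Discussion places them in the sessions. A baseline-only reading is not available from the text. In Data collection and follow-up, "Clinical information will be collected prior to the initiation of CRRT", but the items listed there include no blood gas, pH or phosphate. Blood gases and electrolytes are recorded every 6 h during treatment.

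**3. Whether mode can affect them.** Reading the sections together:

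- Acid-base status: acidosis and alkalosis are outcomes to be assessed, and mode is expected to alter citrate dose and citrate-related events. After the first adjustment, in-session chemistry can also be downstream of earlier post-filter iCa, which is the outcome itself.
- Phosphate: no section says that mode changes it.
- At 2 h: both modes start with the same blood flow, citrate rate, calcium rate, bicarbonate formula and 30 ml/kg/h dose, and citrate is first reassessed at 2 h. A difference produced by titration is therefore unlikely at that sample. The concern lies mainly with later values.

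**4. Illustration of size.** Write dY for the within-patient difference in iCa and dM for the difference in one in-session covariate, scaled to SD 1. Let mode shift dM by a = 0.5 (assumption), and let a share s of the total effect run through it (assumption):

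dY = 0.135 × (1 - s) + b × dM + error, with b = s × 0.135 / a and residual SD 0.2.

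The adjusted contrast estimates 0.135 × (1 - s) rather than 0.135. If an unmeasured factor loads 0.5 on both dM and the error (assumption), the slope is off by 0.2 × 0.5 × 0.5 = 0.05, and the adjusted contrast falls by a further 0.05 × 0.5 = 0.025. Simulated results, n = 26, 4,000 runs per cell:

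| Assumed share s | Adjusted estimate (power), no shared cause | Adjusted estimate (power), shared cause |
|---|---|---|
| -25% | 0.168 (94%) | 0.145 (89%) |
| 0 | 0.135 (82%) | 0.110 (69%) |
| 10% | 0.122 (73%) | 0.097 (57%) |
| 25% | 0.101 (59%) | 0.078 (41%) |
| 50% | 0.068 (31%) | 0.043 (16%) |

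The unadjusted contrast averaged 0.134 to 0.136 in every cell. In the row with no mediation and no shared cause, the adjusted estimate is still right, but power drops from 91% to about 82% because the covariate is correlated with mode. The shares, the shift of 0.5 and the loading of 0.5 are not in the documents. The table shows that the answer depends on them, not what it is.

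**The case against.** The strongest reply is that the adjustment appears only in the Discussion, as an addition, and is never called primary. The Statistical analysis section gives unadjusted paired tests, and the sample size fits them. An unadjusted test with a supporting adjusted model is ordinary practice, and the model details may sit in an analysis plan that is not shown. This stands in part: the two sections can be read as complementary, so they are not an outright contradiction. It does not settle which result carries the conclusion, and the Discussion presents the adjusted analysis as making the conclusions more reliable.

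A reader might also infer more than the documents support:

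- *That mode changes all three covariates, so the adjusted effect is biased.* The documents treat acid-base disturbance as a possible result of mode, in conditional terms, and say nothing of the kind about phosphate. Bias is possible, not shown.
- *That adjustment shrinks the effect, for example to 0.108-0.068 with power of 0.75-0.38 if 20-50% of it is mediated.* That share and its sign are invented, and those powers hold the SD at 0.2. Under Table 1, higher post-filter iCa leads to more citrate, which binds iCa and draws the modes together. Blocking that feedback could enlarge the difference instead. Citrate load is also not among the covariates named.
- *That the 2 h comparison is equally affected.* The identical starting settings argue against this for the titration route.

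**Conclusion.** The point holds in limited form. The Discussion commits to covariates measured after the randomised mode has started. For acid-base status at least, the protocol's own outcomes and titration scheme make it plausible that these values are affected by mode. A contrast adjusted for them need not estimate the total mode effect, chiefly after the 2 h sample. The direction and size cannot be derived; the tabulated range of 0.043 to 0.168 around 0.135 rests entirely on assumed inputs. The practical harm depends on whether the adjusted result is used as the main one, which the text leaves open. Randomised order already protects the unadjusted contrast, so validity does not require the adjustment.

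**What to change.** 1. In the Statistical analysis section, state that the within-patient contrast between modes, without in-session covariates, is the primary analysis. The stated 26 applies to this contrast provided that 0.2 is the SD of the within-patient difference; the section should say so.
2. Report in-session pH, acid-base status and phosphate by mode, as outcomes.
3. Amend the Discussion so that any adjustment for in-session values is labelled exploratory.
4. If a supporting adjusted analysis is wanted, restrict it to values taken before each session starts. One value per patient would not serve, because its additive effect is the same in both sessions and cancels in the difference.

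Items 1 to 3 cost only wording. Item 4 is optional and needs a pre-session value recorded for each session. The planned enrolment of 30 need not change.
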